# Randomised controlled pilot feasibility trial of an early intervention programme for young infants with neurodevelopmental impairment in Uganda: a study protocol

**DOI:** 10.1136/bmjopen-2019-032705

**Published:** 2019-10-09

**Keywords:** neonatal encephalopathy, Uganda, outcomes, impairment, neurodevelopment, cohort study

## Abstract

**Introduction:**

Early intervention programmes (EIPs) for infants with neurodevelopmental impairment have been poorly studied especially in low-income settings. We aim to evaluate the feasibility and acceptability of a group participatory EIP, the ‘ABAaNA EIP’, for young children with neurodevelopmental impairment in Uganda.

**Methods and analysis:**

We will conduct a pilot feasibility, single-blinded, randomised controlled trial comparing the EIP with standard care across two study sites (one urban, one rural) in central Uganda. Eligible infants (n=126, age 6–11 completed months) with neurodevelopmental impairment (defined as a developmental quotient <70 on Griffiths Scales of Mental Development, and, or Hammersmith Infant Neurological Examination score <60) will be recruited and randomised to the intervention or standard care arm. Intervention arm families will receive the 10-modular, peer-facilitated, participatory, community-based programme over 6 months. Recruited families will be followed up at 6 and 12 months after recruitment, and assessors will be blinded to the trial allocation. The primary hypothesis is that the ABAaNA EIP is feasible and acceptable when compared with standard care. Primary outcomes of interest are feasibility (number recruited and randomised at baseline) and acceptability (protocol violation of arm allocation and number of sessions attended) and family and child quality of life. Guided by the study aim, the qualitative data analysis will use a data-led thematic framework approach. The findings will inform scalability and sustainability of the programme.

**Ethics and dissemination:**

The trial protocol has been approved by the relevant Ugandan and UK ethics committees. Recruited families will give written informed consent and we will follow international codes for ethics and good clinical practice. Dissemination will be through peer-reviewed publications, conference presentations and public engagement.

**Trial registration number:**

ISRCTN44380971; protocol version 3.0, 19th February 2018.

Strengths and limitations of this studyThis pilot feasibility trial is among the first to examine feasibility and acceptability of an early intervention programme for young children with neurodevelopmental impairment in a low-resource sub-Saharan African setting.The mixed-method evaluation of this complex community-level intervention will provide important information on implementation of an early intervention programme for child disability at scale.While the small sample size and individually randomised trial design will limit our understanding of programme impact, quantitative and qualitative data will inform design and execution of a larger future trial to examine effects on important child and family outcomes.

## Introduction

Globally each year, an estimated 30 million neonates experience complications around the time of birth which can have a life-long impact on health and development.^1^ The United Nations Global Strategy for Women’s, Children’s and Adolescents’ Health (2016–2030) advocates the need for all children to ‘survive’ and to ‘thrive’.^1^ While in recent decades substantial progress has been made in reducing child mortality in low-income and middle-income countries (LMICs), the global burden of developmental disabilities remains unchanged.^2^ Child neurodevelopmental impairment (NDI) significantly impacts families in any context, but particularly in low-resource settings, where availability and access to support services are limited, financial barriers greater and social stigma more overt.^3^

A wide spectrum of impairment is seen after newborn illnesses, including cerebral palsy, ineffective feeding, learning, visual and hearing difficulties and epilepsy.^4^ A growing evidence base, largely from high-income countries (HICs), suggests that early intervention programmes (EIPs) commencing in the first months after birth have the potential to limit and even prevent developmental and cognitive impairments following early brain injury. These programmes target the neuroplasticity of the immature developing brain, either directly or indirectly, through family capacity building and enrichment of the care-giving environment.^5^

In HICs, it has been shown that early environmental enrichment can enhance motor function in children<2 years.^4 6^ In LMICs, several trials have shown positive effects of EIPs in at-risk infants,^7–10^ although these studies have not focused on infants specifically with NDI. Few studies have examined the feasibility and acceptability on affected children and their caregivers, and how they might be integrated into existing community health programmes.^11^ Scalability and sustainability of an intervention programme are also dependent on its cost effectiveness. This is particularly true in LMICs where resources are scarce and existing care structures for children much less well established.

### Aims

The study aims to evaluate whether a facilitated, community-based, participatory EIP is feasible and acceptable. We will conduct a pilot feasibility single-blind, randomised controlled trial (RCT) with two parallel groups. The outcomes of interest are feasibility of randomisation and recruitment, acceptability among caregivers and healthcare workers and early evidence of family impact quality of life (QoL), 6 months after recruitment and again 6 months later. The incremental and protective cost effectiveness of the EIP and the economic impact of child developmental disability to families and services in Uganda will be examined by [name] *et al* in a separate protocol.

### Objectives and hypotheses

The primary objectives of the study are to

Describe the feasibility and acceptability of the EIP for children with NDI and their families.
***Hypothesis***
*: It will be feasible to conduct an RCT of the EIP versus standard care (SC) in rural and urban contexts and acceptable to families and the community*.Obtain preliminary data on whether the EIP improves family QoL when compared with SC.
***Hypothesis***: *Families receiving the community-based EIP will demonstrate improved QoL scores on the Paediatric Quality of Life Family Impact module compared with SC 12 months after recruitment*.Identify the main barriers and facilitating factors for scaling up the EIP.
***Hypothesis***
*: The EIP is scalable in this low-resource Ugandan setting*.Determine the incremental and protective cost effectiveness of the ABAaNA EIP.
***Hypothesis***: *The ABAaNA EIP is a cost-effective intervention to improve family QoL for children with NDI*.

## Methods

We will conduct a pilot feasibility, single-blind, RCT with two parallel groups: one receiving the EIP and the other SC.

### Study setting

The study is based at two Ugandan sites: one urban (Mulago Hospital, Kampala) and one rural (Kiwoko Hospital, Nakaseke). Neither site has existing family support services for children with NDI.

Mulago National Referral Hospital is the largest in Kampala, Uganda’s capital city, taking high-risk pregnancies from across surrounding areas. Children’s services include acute admissions, an inpatient malnutrition unit and outpatients, with a weekly paediatric neurology clinic providing investigation and management of neurological conditions including seizures, and a clinic-based physiotherapy and occupational therapy service for children with cerebral palsy and other NDIs.

Kiwoko Hospital in Nakaseke District, central Uganda, serves a catchment area of 800 000 people and provides comprehensive medical services, including neonatal inpatient care for >1200 infants per year. The trial implementation partner, Adara Development, has worked in partnership with Kiwoko Hospital since 1998, and the government to improve neonatal health in Nakaseke district. Together they provide HIV services, maternal health services and community-based healthcare to 44 villages surrounding Kiwoko Hospital.

### Participants and recruitment

Participants will be young children with NDI and their caregivers. A Standard Protocol Items: Recommendations for Interventional Trials diagram showing the planned flow of participants is presented in figure 1.

**Figure 1 F1:**
[figure not shown]
Flow of participants. *In-depth interviews (IDI) with caregivers on impact of disability, confidence level of the parents, level of participation in family and community life and experience of stigma/discrimination. EIP, early intervention programme; GMDS, Griffiths Mental Developmental Scales; HINE, Hammersmith Infant Neurological Examination; HOME, Home Observation for the Measurement of the Environment; MDAT, Malawi Developmental Assessment Tool; MIRI, Maternal Infant Responsiveness Inventory; NDI, neurodevelopmental impairment; PedQL, Pediatric Quality of Life tool; PEDI, Pediatric Evaluation Disability Inventory; PSI, Parent Stress Index; SRQ, Self-Referral Questionnaire.

#### Screening for eligibility

Infants at high-risk of NDI will be identified from (1) neonatal admission registers and neonatal follow-up services, (2) local paediatric outpatient services and (3) attendance for early child health services following community sensitisation. Sensitisation will include public health announcements on local radio raising awareness of the research and appropriate child development more generally. Caregivers of high-risk infants (survivors of neonatal encephalopathy, prematurity, neonatal septicaemias/meningitis and severe jaundice) will be contacted by phone and invited to attend an appointment when the child is 6–11 completed months old. After informed written consent, they will be screened for NDI by trained study staff using the Malawi Developmental Assessment Tool (MDAT).^12^ If two or more items in any MDAT domain are not achieved, the child will be referred for comprehensive neurodevelopmental assessment. If the child fails one item in two or more domains, they will be invited back for an assessment in 1 month. If the child’s MDAT scores are age appropriate across all domains, advice will be given on play and stimulation, communication, nutrition and immunisations and the child discharged.

Caregivers of infants screening positive on MDAT will be invited to an appointment for written informed consent, and if provided, comprehensive neurodevelopmental assessment by study staff using the Griffiths Mental Developmental Scales (GMDS)^13^ and the Hammersmith Infant Neurological Examination (HINE).^14^ An overall developmental quotient will be derived, from the GMDS subscales assessing locomotor, personal–social, hearing/language, eye-hand coordination and performance skills.^13^ Neuromotor impairment will be further assessed according to the HINE, a standardised paediatric neurological examination and classified by type. We have used both these tests extensively in previous studies in Uganda and found them easy to administer in this setting and at this age.^15^ The assessments will be conducted in the local language using the standard manual material to ensure internal consistency in the assessments technique. Inclusion and exclusion criteria are outlined in box 1.

Box 1Eligibility for inclusion in the randomised controlled trialInclusion criteriaInfant aged 6–11 completed monthsModerate–severe neurodevelopmental impairment (NDI) defined as a Griffiths Mental Developmental Scales (GMDS) Developmental Quotient <70 and/or Hammersmith Infant Neurological Examination (HINE) score <60 (Romeo, 2013)Informed written consent by caregiverExclusion criteriaInfants aged 12 months of age or olderInfants screening positive for NDI (using Malawi Developmental Assessment Tool) but not meeting the criteria for moderate–severe NDI on GMDC and HINE assessmentConditions requiring prolonged inpatient treatmentParents unwilling or unable to attend the full programmeMain residence outside Nakaseke or Luwero district, and >20 km from Mulago HospitalAccompanying caregiver not speaking or understanding Luganda or English

### Baseline characteristics

Infant and caregiver demographic information will be recorded at baseline, including date of birth, age, sex, birth order, parity, antepartum, intrapartum and postpartum history, family and medical history, developmental history, mother’s education and occupation, family details including family size, and ages, household incomes, household SES and residence. All outcome measures will also be measured at baseline enabling preintervention and postintervention comparisons.

### Randomisation

Infants and their caregivers will be randomised in a 1:1 ratio to either the EIP or SC arm. Randomisation will be stratified by recruitment centre. Randomisation lists indicating a randomisation number and trial arm allocation will be prepared by the trial statistician using a random number generator in Stata (V.15) prior to the commencement of the study, and stored on a secure, password-protected computer at the Medical Research Council/Uganda Virus Research Institute (MRC/UVRI) and London School of Hygiene & Tropical Medicine (LSHTM) Uganda Research Unit by a statistician otherwise not involved in the study. When a participant is eligible for recruitment and consent obtained, study staff will contact the MRC/UVRI statistician who will inform the study staff of the study number and trial arm to which the participant is to be allocated. The personnel in charge of the randomisation will not be involved in other study procedures, including assessment of outcomes.

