### Outcomes

Participants in both arms will be assessed by study staff masked to trial allocation at two time points; at age 12–17 months (which corresponds to completion of the EIP in the intervention arm, 6 months after recruitment) and again at age 18–23 months (12 months after recruitment). (figure 1). Caregivers will be phoned a week before the follow-up assessments to arrange a time for interview. Assessments will be primarily conducted in the study-site clinics. Where caregivers cannot be contacted by phone or are unable to attend the clinic, a community visit will be arranged, and assessments completed at home. Outcome assessments will be conducted by Mulago assessors for children recruited at Kiwoko, and vice versa to ensure assessors are blind to allocation arm. Two assessors will independently assess a small proportion of the children and inter-rater reliability will be calculated.

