### Statistical analysis

The first primary outcome, feasibility of participant recruitment and randomisation, will be assessed by the total number recruited and randomised to each arm. Recruitment and randomisation feasibility will be demonstrated if the target sample size of 126 is achieved. Data on participants screened, eligible and randomised will be displayed in a Consolidated Standards of Reporting Trials flow chart. Descriptive statistics (frequencies, means, medians, SD and IQRs) will be used to describe the sample at baseline, by trial arm.

The second primary outcome, acceptability, will be assessed quantitatively by (1) calculating the protocol violation rate and (2) summarising the number of programme sessions attended between baseline and programme completion for those in the intervention arm. Protocol violation rate will be calculated as the number of participants for whom one or more protocol violations occur divided by the total number of participants, and will be presented both overall, and by trial arm. For participants in the EIP trial arm, the overall number of modules attended by each participant will be tabulated. Acceptability on the basis of number of programme sessions will be defined as attendance of at least six modules.

For the third primary outcome and secondary outcomes, analyses will compare outcomes between intervention and control arms at the end of the programme, when the participants will be aged 12–17 months, and again 6 months later. Analysis will be on an intention-to-treat basis and missing data will not be imputed. Data for each outcome measure will be summarised by trial arm, using proportions for binary outcomes and means or medians for quantitative outcomes, depending on normality of the distribution. Differences in means/proportions between trial arms together with 95% CIs will be calculated. We do not plan any formal statistical tests due to the preliminary nature of the trial; instead CIs will provide a possible range of effect sizes. Regression models (linear regression for continuous outcomes, logistic regression for binary outcomes) will be used to adjust comparisons for baseline measures of the outcomes, which were collected at enrolment into the trial, in order to improve precision of effectiveness estimates. For skewed continuous outcomes, data will be normalised before analysis using suitable transformations or quantile regression will be considered. No subgroup analyses are planned.

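### Randomisation is stratified by centre, but the regression models name only the baseline outcome as covariate; the cost is some precision, not bias

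*Protocol article*

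**What the plan says.** Protocol article, Randomisation: "Infants and their caregivers will be randomised in a 1:1 ratio to either the EIP or SC arm". On how the lists are structured, the same section adds: "Randomisation will be stratified by recruitment centre". No other stratification factor is named, and blocks are not mentioned. Under Study setting there are two centres, one urban (Mulago) and one rural (Kiwoko).

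Protocol article, Statistical analysis, for family quality of life and the secondary outcomes: "Differences in means/proportions between trial arms together with 95% CIs will be calculated". Linear or logistic regression models "will be used to adjust comparisons for baseline measures of the outcomes", and the stated reason is "in order to improve precision of effectiveness estimates". Centre is not named as a covariate or stratum in any analysis, and the article does not say whether the crude or the adjusted difference is the main result. On inference: "We do not plan any formal statistical tests due to the preliminary nature of the trial; instead CIs will provide a possible range of effect" […].

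Protocol article, Outcomes: "Outcome assessments will be conducted by Mulago assessors for children recruited at Kiwoko, and vice versa to ensure assessors are blind to allocation arm".

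**The concern.** When allocation is balanced within a factor that predicts the outcome, a model without that factor counts the between-level variation as noise, and the interval for the arm difference is wider than the design warrants. Here the adjustment is made explicitly for precision, yet the one factor built into the randomisation is left out of the stated covariates.

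There are two reasons why centre could matter. First, the sites differ in setting and partly in services: Mulago is a national referral hospital with a weekly neurology clinic and clinic-based therapy, while Kiwoko is rural with community-based care. Second, the exchange of assessors makes centre and follow-up assessor team the same variable, and PedsQL is administered as an interview by study staff. The exchange is described for outcome assessments only. If local staff do the baseline interviews (the article does not say), the baseline score cannot absorb a team difference that arises at follow-up.

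Confidence intervals are the only inferential output, so their width is what will inform a larger trial.

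**Working it through.** **1. The plan's own figure.** Inputs from Sample size: control mean 65, relative difference 20%, SD 20, 5% significance (two-sided assumed), 90% power, 20% dropout.

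- Difference = 0.20 × 65 = 13 points.
- n per arm = 2 × (1.960 + 1.282)² × 20² / 13² = 49.7, so 50.
- 50 / (1 − 0.20) = 62.5, so 63 per arm and 126 in total.

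This matches the article. The calculation is for a crude comparison, so adding centre to the model does not change it.

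**2. Assumptions not in the article.** Centre difference d of 5 to 12 points; two equal centres; within-centre correlation of baseline and follow-up 0.5; 50 analysed per arm.

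- Residual variance with baseline and centre in the model = 400 × (1 − 0.5²) = 300.
- Variance from a difference d between two equal centres = d²/4.

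**3. Centre difference not visible at baseline** (for example, a follow-up team difference). The full d stays in the error term, and the CI-width ratio is √(1 + (d²/4)/300).

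**4. Same centre difference at baseline and follow-up.** A baseline slope of about 0.5 removes about half, leaving d/2, and the ratio is √(1 + (d²/16)/300). The fitted slope would sit slightly above 0.5, so this slightly overstates the excess.

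| d (points) | Ratio, not visible at baseline | Ratio, same at baseline |
|---|---|---|
| 0 | 1.000 | 1.000 |
| 5 | 1.010 | 1.003 |
| 8 | 1.026 | 1.007 |
| 10 | 1.041 | 1.010 |
| 12 | 1.058 | 1.015 |

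In points: the CI width with centre in the model is about 2 × 1.96 × √(300 × 2/50) = 13.6. The largest excess in the table is 0.058 × 13.6 = 0.8 points of total width, or 0.4 on each side, against a target difference of 13.

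**5. Check by simulation.** There were 5,000 runs per scenario, with 100 analysed, total SD held at 20, true effect 13 and arms balanced within centre. Each cell gives the mean 95% CI width, then the coverage.

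| Scenario | Baseline only | Baseline + centre |
|---|---|---|
| d = 0 | 13.8, 95% | 13.8, 95% |
| d = 5, not visible at baseline | 13.8, 95% | 13.7, 95% |
| d = 10, not visible at baseline | 13.9, 96% | 13.4, 95% |
| d = 20, not visible at baseline | 14.4, 98% | 11.9, 95% |
| d = 10, same at baseline | 13.5, 95–96% | 13.3, 95–96% |
| d = 20, same at baseline | 12.4, 96% | 11.9, 95% |

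The simulated ratios agree with the formula: at d = 10 not visible at baseline, 13.94/13.36 = 1.043 against 1.041. The mean estimate from the baseline-only model lay between 12.9 and 13.1 in every scenario, so there was no bias. The crude CI was about 15.8–15.9 wide throughout.

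**The case against.** The strongest reply is that the article condenses a longer protocol, does not say that baseline is the sole covariate, and may be completed by an analysis plan that includes centre and ranks the estimates. That is possible. But the article does state model type, covariate and purpose, and the set it states omits the only stratification factor. If another document adds centre, the published text needs aligning with it.

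Second, the effect is small and conservative. This stands. The article gives no centre difference, so every figure above is conditional on an assumed one. Standard care at both sites includes referral to physiotherapy, seizure management and nutritional support, and neither site has family support services. The PedsQL interview is standardised, inter-rater reliability will be checked, and each team assesses both arms.

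A reader might infer stronger versions that the article does not support:

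- *The arm difference is biased.* Allocation is randomised within centre, so the linear estimate is unbiased with or without a centre term.
- *The intervals are necessarily too wide for the design.* Over-coverage needs arms balanced within centre. Blocks are not mentioned, and with unblocked lists coverage would be about nominal. Adding centre would still gain precision.
- *Dropout could shift the result by a point.* A 60:40 centre split in one arm against 50:50 in the other, with a 10-point centre difference, moves the crude contrast by 0.10 × 10 = 1 point. From equal centres (31.5 per arm and centre), reaching 30 and 20 in one arm needs losses of 1 − 30/31.5 = 5% and 1 − 20/31.5 = 37%, while the other arm loses 20% at both. That pattern is extreme. The shift applies to the crude contrast and is a quarter of its standard error, 20 × √(2/50) = 4.

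**Conclusion.** The mismatch stands as a question of precision. The stated models leave out the stratification factor, so any centre difference beyond what the baseline score carries, including one between assessor teams, goes into the error term. With an assumed centre difference of 5 to 12 points, SD 20, correlation 0.5 and equal centres, the CI is about 0.3–1.5% wider than it need be if the same difference is present at baseline, and about 1–6% if it is not visible at baseline. Mild over-coverage follows only if arms are balanced within centre. If the centres do not differ, there is no loss. The linear estimate is unbiased and the sample size of 126 stands.

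The lack of a named main estimate is a secondary matter. It is worth settling in the same sentence because, under these assumptions, the crude interval is visibly wider than the adjusted one (about 15.8 against 13.8 points with no centre difference).

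**What to change.** In Statistical analysis, state that the between-arm linear and logistic models include recruitment centre (two levels, fixed) alongside the baseline value of the outcome. Name the centre- and baseline-adjusted difference with its 95% CI as the main estimate for PedsQL Family Impact, and give the crude difference as supportive. For the logistic models, note that the odds ratio is then conditional on centre, so it is not the same quantity as the odds ratio without it.

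The cost is one or two sentences and one degree of freedom. Centre is already recorded, and no participants, visits or data items are added. If an analysis plan already specifies this, only the published wording needs to be aligned.
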